### Patient follow-up

The respondent burden will be kept to a minimum. The research team will contact patients by telephone within four days to offer further information about study participation and to iron out eventual problems concerning study materials. Reminders to complete study documents will be sent by post to patients after 14 days, and patients will receive a reminder postcard at the end of the follow up period.

### Analysis

Statistical analyses will be performed with the aid of the SPSS and STATA statistical packages. The primary analysis will be intention to treat and will compare the marginal effects of the two interventions on antibiotic prescribing at the index consultation and incorporate an interaction effect. The interaction term will be included to test for a synergistic or antagonistic relationship between the two interventions. This will be tested using a three level logistic regression model to account for variation at the practice/GP/patient. If there is no indication of random effects at a GP level, then this will be reduced to a two level model with GP seen acting as a patient level covariate.

A four level linear regression model will be fitted to the symptom scores (logged) to account for practice, GP, patient and repeated assessments over time. The correlation between repeated assessments within individual patients will be modelled to allow for greater correlation between assessments, which are closer in time. The effect of interventions would be seen in the comparison of the slopes of symptom scores over time in the groups, i.e. having faster (or slower) recovery rates[38]. Sensitivity analyses on the symptom scores will be undertaken to assess the impact of loss to follow-up by either interpolating from available data using the estimated slope of symptoms from the model or using last value carried forward. The later is unlikely to arise in practice for an acute infection, however provides a useful extreme bound in which to interpret results.

Secondary outcomes (satisfaction, enablement, re-consultation and other investigations) will be compared between the two groups using three level regression models (linear and logistic where appropriate). No formal sub-group analyses are planned. However, exploratory analyses will investigate the influence of patient and practitioner demographics on outcomes. The statistical uncertainty regarding the cost-effectiveness of the different strategies will be assessed using non-parametric bootstrap resampling techniques and result in estimates of net monetary benefit values. For the groups of GPs trained in enhanced communication skills and/or CRP testing, the cost analysis will be extended beyond patient level data. Training will lead to additional costs (organising and giving the training and GPs' time investment) which will be included in the analysis[39]. Such overhead costs are basically one-time costs and can therefore be regarded as fixed costs that will be measured at the level of the trained GPs and attributed to an individual patient, which will be done on the basis of a division calculation as proposed by Mason et al (2001)[40]. The trial will be reported following CONSORT guidelines, extended for cluster randomised trials[41].

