### Sample size calculation

In order to detect a reduction in antibiotic prescribing from 80% to 60%, with 80% power at a 5% significance level, an individually randomised study would require 175 patients. If we randomise 20 practices with an intra-cluster correlation coefficient (icc) of 0.06 this increases to 350 patients. In order to allow for a 90% follow-up rate for the primary outcome measure of antibiotic prescribing we intend to recruit 400 patients (20 per practice and 100 in each cell). We have previously demonstrated that 40 GPs can recruit over 400 patients suspected of having a LRTI in two winter seasons[11].

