We chose a factorial design, as it will enable us to efficiently investigate the interventions by including all participants in both analyses. Furthermore it will give us the opportunity to consider both the individual effects of both interventions and the benefits of receiving both interventions together. Factorials trials do require special considerations at the analysis stage. Interaction between the interventions needs to be investigated, since this can have effect on the power of the study[42].

In this trial both interventions are targeted at the GPs with impact on patient outcomes. Randomisation at practice level has been chosen in this trial, because there is less risk of contamination by GPs concurrently managing usual care patients, while other GPs manage their patients under the experimental regimen in the same practice. However, since patients yet have to be recruited after randomisation post-randomisation recruitment bias deserves special attention. One may expect that practices not receiving a desired intervention may gradually loose enthusiasm to recruit. As a strategem to prevent this, those practices allocated to the usual care arm, as well as those allocated to one of the arms to which only one intervention will be allocated, will be informed that they will receive a CRP device and/or the communication training after the study period. Recruitment rates across the four groups have to be monitored and baseline characteristics will be described to ensure comparability. Because of the small number of practices involved, randomisation will be restricted carefully with regard to recruitment ability. With a small number of clusters and a large number of patients this trial may be difficult to analyse and risk of loss of power exists if one practice should drop out. In cluster randomised trials the outcome for each patient cannot be assumed to be independent of that of any other patient since the patients within one cluster (practice) are more likely to have similar outcomes. Therefore multi-level analysis will be performed.

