Prediction of sample size in cluster randomised trials is difficult given the fact that not only the expected effect size has to be estimated, but also the anticipated cluster size and intra-cluster correlation coefficient[43]. Despite these limitations analysis on both cluster level as well as individual level will provide us the best information on the outcome of this study[44]. Results will be reported with full transparency with regard to the factorial and cluster design[41,42].

The study will allow us to get more insight into the natural course of this common but still under-researched illness. The long follow-up of 28 days and the daily patients' evaluation of number and extent of their symptoms will provide crucial information on natural course, burden and impact on daily activities.

To our knowledge, both from the point of view of interventions and study design, this is a unique study. It will be the first to evaluate complex interventions separately and combined, that focus on the biomedical evaluation of the illness and patient centered communication. The pragmatic nature of the study, which leaves treatment decisions up to the responsible clinicians, will enhance the applicability and generalisability of findings. If these interventions decrease antibiotic prescribing and enhance patient satisfaction with favourable clinical outcomes, they could be used to enhance the quality of a large number of consultations in primary care, both for common infections and for other conditions. A full cost-effectiveness analysis to evaluate the efficiency of the interventions is needed in this regard as well and will therefore be performed. This has never been done before for an intervention to improve health care providers' communication regarding antibiotics prescribing.

If these complex interventions are shown to be effective and cost-effective, they may be refined as a result of the research and we will promote uptake in everyday care.

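### The primary multilevel logistic test on 20 practices names no small-cluster correction; under ordinary maximum-likelihood inference its nominal 5% level would be about 8-10% (Wald) or 6-8% (likelihood ratio).

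*Protocol article*

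**What the plan says.** The Analysis section of the protocol article compares the marginal effects of CRP testing and communication training on prescribing at the index consultation, with an interaction term. On the method it says: "This will be tested using a three level logistic regression model to account for variation at the practice/GP/patient". If there is no sign of GP-level variation, the model drops to two levels. SPSS and STATA are named as packages. No estimator, reference distribution or small-sample method is given.

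The Sample size calculation section plans for 80% against 60% prescribing, "with 80% power at a 5% significance level". It assumes 20 practices and an ICC of 0.06.

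The Discussion sees that there are few clusters: "With a small number of clusters and a large number of patients this trial may be difficult to analyse". The consequences it names are difficulty of analysis and loss of power if a practice drops out; the false-positive rate is not mentioned. It adds that "analysis on both cluster level as well as individual level will provide us the best information on the outcome of this study", without defining the cluster-level analysis.

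**The concern.** The treatment contrast is between practices, ten against ten at each margin, so the number of practices and not the number of patients governs how well its standard error is known. Ordinary maximum-likelihood output for a multilevel logistic model ignores this in two ways. It refers the estimate to a normal or chi-square distribution, as if the standard error were known. It also tends to underestimate the between-practice variance when clusters are few. Both errors make the test too liberal and the interval too narrow.

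At stake is the error rate of both main comparisons and of the interaction test in an open trial. A test presented at 5% could carry nearly twice that risk of a false positive.

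**Working it through.** **Inputs from the article.** 20 practices, 5 per cell and 10 against 10 at each margin; two GPs per practice; 80% v 60%; 80% power; 5% level (taken as two-sided, which is not stated); ICC 0.06; 400 recruited and 90% followed up, so 360 analysed, or 18 per practice.

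**The plan's own figures.**
- Individually randomised total (stated: 175). The log-odds formula gives (1.96 + 0.842)² × (1/0.16 + 1/0.24) / (ln 2.667)² = 85 per arm, or 170 in total. The pooled two-proportion formula gives 164, and 182 with continuity correction. The stated 175 lies within this range.
- Clustering: 175 × [1 + (17.5 - 1) × 0.06] = 175 × 1.99 = 348, against the stated 350.
- Follow-up: 350 / 0.9 = 389, rounded up to 20 × 20 = 400.

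The sample-size arithmetic is not at fault.

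**Degrees of freedom.** The intercept, two main effects and interaction are four practice-level terms: 20 - 4 = 16 (17 if the interaction is dropped).

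**Analytic check of size.**
- Reference distribution alone: P(|t16| > 1.96) = 6.8% (t17: 6.7%).
- Adding a rough allowance for variance underestimation (division by 20 instead of 16): the effective threshold is 1.96 × √(16/20) = 1.753, and P(|t16| > 1.753) = 9.9%.
- Interval width: the t16 multiplier is 2.120. Using 1.960 makes the interval narrower by 1 - 1.960/2.120 = 8% before any variance bias.

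**Simulated size under the null.** 3,000 trials per scenario, maximum-likelihood fits by Gauss-Hermite quadrature, ICC 0.06, 18-20 patients per practice, base rate 0.6-0.8, with or without GP-level variance, equal or unequal practice sizes. Simulation error is about 0.4-0.5 points.

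| Test at nominal 5% | Actual size |
|---|---|
| Three-level with interaction, Wald z, main effects | 8.1-9.4% |
| Three-level with interaction, Wald z, interaction | 7.6-9.1% |
| Two-level with interaction, Wald z, main effects | 8.7-9.7% |
| Two-level without interaction, Wald z | 7.9-8.6% |
| Two-level without interaction, likelihood ratio | 6.3-7.6% |
| Two- or three-level with interaction, same fit on t16 | 6.0-7.4% |
| Practice-level regression with interaction, t16 | 5.0-5.2% |

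Sensitivity to the ICC (three-level Wald, main effects): 7.3% at 0.02 and 9.9% at 0.12. A separate, smaller simulation of the two-level model with interaction gave about 10% for Wald z (standard error about 1 point) and about 6% for the practice-level t test.

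**Power for 80% v 60%, 180 analysed per margin.** Design effect 1 + 17 × 0.06 = 2.02. SE = √[(0.16 + 0.24) × 2.02 / 180] = 0.0670. Ratio 0.20 / 0.0670 = 2.985. Power is 0.847 against z and 0.800 against t16. With 350 analysed the figures are 0.843 and 0.795; with 400, 0.864 and 0.818.

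Simulated power of practice-level regression was 0.73-0.76 with random-intercept variance 0.21-0.36 (main effects only, 17 df). In another simulation it was 0.80.

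**The case against.** The strongest reply is that the article is silent, not wrong. It specifies neither maximum likelihood nor a Wald z test and excludes no correction, and estimator and degrees of freedom are often left to an analysis plan, which is not shown. This stands as a limit on the wording. A reader might infer that the protocol has chosen an uncorrected test and that its 5% level is in fact inflated; the text does not support that. The inflation is what the stated model gives when run in its usual maximum-likelihood form. What remains is that the article fixes the model down to its fallback and raises the small number of practices itself, yet does not address their effect on the error rate.

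The size also depends on the test: a likelihood-ratio test is milder than Wald z. That is fair, but it too exceeds 5%.

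A reader might further infer that the Discussion's mention of cluster-level and individual-level analyses leaves two unranked analyses from which the favourable one could be picked. The documents do not support this. The Analysis section attaches the multilevel model to the primary analysis, and the Discussion confirms that a multilevel analysis will be performed. The cluster-level remark does not set up a competing primary test.

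**Conclusion.** The point holds in conditional form. As written, no small-cluster correction is named for the primary test. With ordinary maximum-likelihood inference on 20 practices, a nominal 5% test of either intervention runs at about 8-10% with Wald z and about 6-8% with a likelihood-ratio test, and the intervals are too narrow.

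The result assumes a maximum-likelihood fit with a large-sample reference, which the article neither states nor excludes. It does not hinge on the exact ICC: the Wald test was liberal at every value tried from 0.02 to 0.12. It applies to the three-level model and to its fallback. The Discussion's acknowledgement of few clusters does not cover it, because the consequences named there are difficulty and lost power.

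**What to change.** In the Analysis section, state that the primary p-value and confidence interval use practice-level degrees of freedom, with the planned interaction kept. Name one of these routes in advance:

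1. Regress the 20 practice prescribing proportions on CRP, communication and their interaction, with t on 16 df. This held 4.8-5.3% across all simulated scenarios, including the other ICC values. It reports a difference in proportions, not an odds ratio.
2. Keep the multilevel model, but with restricted (bias-corrected) variance estimation and a small-sample t reference such as Satterthwaite or Kenward-Roger. This route was not simulated here, so its size should be checked before it is adopted.

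Referring a maximum-likelihood fit to t16 is not enough.

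The change takes a sentence or two and no extra patients. It costs about 5 points of analytic power (0.85 to 0.80 at 360 analysed and ICC 0.06), so the 80% target is roughly kept; part of the power given up was only the inflated error rate. If the first route is chosen, also disclose its simulated power of 0.73-0.80, which depends on the assumed between-practice variance and can fall short of the target.

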### Patients

The GPs will approach sequential eligible adult patients during regular consultation hours. Patients are eligible if they present in general practice with an acute cough, lasting no more than 4 weeks, considered to be caused by LRTI according to the GP. In addition, the patient needs to have at least one focal and one systemic sign/symptom[33] (Figure 1). Children will not eligible, since the diagnostic value of CRP has not been investigated for LRTI in children, consultations with children and their parents will be different with respect to communication styles and strategies, and diagnostic and prognostic factors are not automatically applicable in infants. Exclusion criteria are described in figure 1.

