### Communication training

The communication training is based upon a patient-centred strategy to achieve shared decisions about investigation and treatment of acute infections. The intervention is based on the elicit-provide-elicit framework, which has its background in motivational interviewing and which has been refined for use in primary care[26]. The context-bound training for acquiring these communicating skills involves one two-hour training seminar at a central location, preceded and followed by consulting with simulated patients in routine surgeries. It involves the following specific elements:

#### 1. Simulated patient in clinical encounter, part 1

Two experienced simulated patients will be trained to simulate a patient with acute bronchitis persisting for two weeks. The patient is worried about the duration of the cough and has distinct sleeping problems and impaired daily activities due to the cough. The simulated patients will consult with participating GPs at their own surgeries during regular surgery hours. The simulated patients will carry an audiotape device to record the conversation, which will be transcribed by trained typists.

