### Data collection

Sequential elegible patients will be asked by their GP to participate. During this consultation, the GP will take written consent and note the inclusion criteria on the trial inclusion form. The practice nurse will give each participant a simple self-complete symptom diary after the consultation. After general questions on cough and the consultation, patients will be asked each day to complete a 6 item scale, with responses to statements ranging from 0 to 6. A total symptom score will be derived from this scale. Items relate to coughing, phlegm, shortness of breath, sleep disturbance, impairment of normal daily activities, and generally feeling unwell. This symptom diary has previously been used in a large LRTI study[35]. Patients will then be followed-up for 28 days, or if still unwell, until recovered with a maximum follow up of ten weeks. Furthermore, weekly questions will record time off work, medication use and re-consultation. The recruiting GP will fax the informed consent form and inclusion form to the research team in Maastricht on the day of inclusion. The clinical effectiveness analysis will be based on diary responses. A single Likert type scale response item will assess satisfaction with the consultation. Patient enablement will be measured using the Patient Enablement Instrument [36] translated into Dutch. Concurrent validation will be undertaken. In addition, the research team will retrieve data on diagnosis, antibiotic prescription, re-consultation, diagnostic testing other than CRP and related medical consumption from participating patients' electronic medical records over 28 days follow-up. A societal perspective will be used for the economic evaluation. Thus, for all four groups, in addition to costs to the health care system, we will take into account medical costs borne by patients and production costs due to illness related absence from work. Use of health care facilities will be prospectively recorded in a standardised way including all re-consultations, telephone consultations, out-of-hours consultations, and hospital admissions, (repeat) prescription of antibiotics (type, dosage, duration) and additional diagnostic tests, including bacteriological culture and X-ray. A patient diary will be the basis for assessing actual medication use, other medical costs to the patient, and absence from work[37].

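### Recovery is compared as slopes of logged symptom scores in patients who enter up to four weeks into a cough; the symptom model should carry cough duration at entry and its interaction with time

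*Protocol article*

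**What the plan says.** The Patients section of the protocol article sets a wide entry window: "Patients are eligible if they present in general practice with an acute cough, lasting no more than 4 weeks". Under Data collection, "The practice nurse will give each participant a simple self-complete symptom diary after the consultation", and "patients will be asked each day to complete a 6 item scale, with responses to statements ranging from 0 to 6". Follow-up lasts 28 days, or up to ten weeks for patients still unwell.

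The Analysis section then states: "A four level linear regression model will be fitted to the symptom scores (logged) to account for practice, GP, patient and repeated assessments over time". It defines the effect on recovery as follows: "The effect of interventions would be seen in the comparison of the slopes of symptom scores over time in the groups".

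The article gives no explicit time origin. Inclusion is the natural reading, because the diary starts there and no other origin is offered. The diary opens with some questions about the cough ("After general questions on cough and the consultation"), but the article does not say whether the number of days since onset is among them. Randomisation is stratified on the practice's recruitment ability only, and the exploratory analyses name only patient and practitioner demographics. The Discussion recognises bias from recruiting after randomisation. It answers with delayed access to the interventions, monitoring of recruitment rates and a description of baseline characteristics, and states no adjustment in the analysis.

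**The concern.** In a self-limiting illness, a patient seen on day 3 has most of the course ahead and one seen on day 20 has little left. A slope fitted from inclusion can therefore depend on when in the illness the patient was enrolled. Practices know their allocation, and their GPs judge eligibility and approach patients afterwards, so the mix of illness stages could drift apart between arms. A difference in stage could then appear as a difference in recovery rate, or hide a real one.

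Clinical recovery is the first secondary outcome and supports the claim that prescribing can fall without harm to recovery. An error in the slope comparison in either direction bears on that claim. Even with balanced arms, stage left out of the model adds patient-to-patient variation in the slopes.

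**Working it through.** The plan states no figure on this point, so there is nothing to reproduce. The documents give no symptom curve and no distribution of prior cough duration; all curves below are assumptions. In each case a least-squares line is fitted to the logged score over about 28 diary days, for patients entering *s* days after onset. Percentages are changes in the size of the slope; negative means flatter, that is, apparently slower recovery.

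**1. Pure log-linear decline, no offset.** Score = 24·exp(-0.08·(s+t)), so log score = log 24 - 0.08s - 0.08t. Entry day *s* enters the intercept only. The slope is -0.080 for every entry day from 3 to 28, so there is no bias.

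**2. Same decline, with an offset for zeros.** The total comes from six items scored 0 to 6, so recovery means a score of 0 and log(0) is undefined. With log(score+1):

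| Entry day | 3 | 7 | 14 | 28 |
|---|---|---|---|---|
| Slope | -0.068 | -0.064 | -0.056 | -0.036 |

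The floor alone makes the slope depend on stage; no plateau is needed. Varying the decline from 0.05 to 0.16 per day, entry on day 8 instead of day 7 makes the slope about 1% to 7% flatter.

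**3. Plateau, then decline, with offset.** Score = 20·exp(-r·max(0, s+t-P)), P = 5, 7 or 10 days, r = 0.08, 0.12 or 0.16 per day, log(score+1), t = 0 to 28, no intervention effect. For P = 7 and r = 0.12 the slopes are -0.0925, -0.0915, -0.0839 and -0.0723 for entry on days 3, 7, 10 and 14; day 10 against day 7 is 0.0839/0.0915 - 1 = -8%. Over all nine curves:

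| Entry compared | Change in slope |
|---|---|
| Day 8 v day 7 | +1% to -5% |
| Day 10 v day 7 | +1% to -16% |
| Day 14 v day 7 | -4% to -38% |
| Day 7 v day 3 | +12% to -15% |

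These treat all patients in an arm as entering on one day. Spreading entry days (assumed SD 6 days, cut off at 28) with nominal means of 9 and 8 days also gives about +1% to -5%.

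**4. A different shape.** Score = 30/(1+exp((s+t-14)/5)):

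| Entry day | 3 | 7 | 14 | 28 |
|---|---|---|---|---|
| log(score) | -0.126 | -0.152 | -0.182 | -0.199 |
| log(score+1) | -0.105 | -0.115 | -0.102 | -0.028 |

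Without an offset, later entry looks like faster recovery; with one, the relation is not monotone. The direction cannot be fixed in advance.

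**5. How large might a chance imbalance be?** SE of the difference in mean duration = SD·√(DE·2/n), with DE = 1 + (20-1)·ICC for 20 patients per practice. Assume an SD of 5 to 8.08 days (the upper value is uniform entry over 28 days, 28/√12) and an ICC for duration of 0 to 0.10. The protocol's 0.06 is for prescribing.

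- Margins, 200 v 200: from 5·√(2/200) = 0.5 days to 8.08·√(2.9·2/200) = 1.4 days.
- Cells of 100: 0.7 to 2.0 days.

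A one-day gap is therefore plausible by chance. A gap of three days or more on the margins would probably need differential recruitment.

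**The case against.** The strongest reply is that this is a condensed article. It gives the structure of the symptom model in a few sentences and lists no fixed-effect covariates for any outcome; that list and the definition of time zero are commonly left to the full protocol or SAP. This stands to the extent that a reader might infer the plan will take no account of time since onset. The article does not say so, and a fuller document may already do it. What remains is that the article fixes the effect measure as a slope comparison in a cohort of mixed illness stage and names the recruitment bias, but for that bias it offers only measures that do not act on the slope. Describing an imbalance does not remove it from the estimate.

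Second, the chosen scale may protect the analysis: under exact log-linear decline there is no bias (step 1). That is correct, and bias needs two things together, an imbalance in stage and curvature or a floor on the log scale. The second is likely with a score that reaches zero within a 28-day diary. The first is possible but not shown, and GPs are to approach eligible patients in sequence.

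Third, a reader might infer that communication-trained GPs will recruit later in the illness because their simulated patient is "a patient with acute bronchitis persisting for two weeks". The documents do not support this. The simulated case serves the consultation training and has no stated role in selecting patients.

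**Conclusion.** The point holds as a worthwhile improvement to a secondary analysis. It does not show an error in the plan, and the primary prescribing outcome is untouched. The slope depends on illness stage at entry whenever logged scores are not linear in time since onset, and the floor at zero makes that likely. An imbalance in stage could then bias the slope comparison in either direction.

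Under the plateau curves with the offset, a one-day difference in mean entry is worth about +1% to -5% of the slope and a three-day difference +1% to -16%; under pure log-linear decline it is worth nothing. The 38% in the working needs a full week's difference between arms, which no figure in the documents supports. It would be too strong to say that an arm difference in stage will be read as a difference in recovery.

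The conclusion rests on the assumed curves, on an offset of 1 in the log, and on inclusion being the time origin, which is inferred from when the diary is handed out. The gain in precision from modelling stage was not quantified.

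**What to change.** In the four-level symptom model, add days of cough before inclusion and its interaction with time as fixed effects. The interaction is the part that matters: a main effect alone shifts the level and leaves the slope comparison as it was. If the inclusion form or the opening diary questions record only that the four-week limit is met, record the number of days. Include prior duration in the baseline comparison by arm that is already planned. Time since cough onset can serve as the time scale in a sensitivity analysis. If a fuller plan already contains these terms, a sentence confirming it is enough.

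The cost is two more fixed-effect terms and at most one number on an existing form. Recall of onset is approximate, and a linear interaction will not fully capture a relation that is not monotone, so the adjustment will be imperfect.

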**Methods/Design:**

This cluster randomised controlled, factorial trial will introduce two interventions in general practice; point of care CRP testing and enhanced communication skills training for LRTI. Twenty general practices with two participating GPs per practice will recruit 400 patients with LRTI during two winter periods. Patients will be followed up for at least 28 days. The primary outcome measure is the antibiotic prescribing rate. Secondary outcomes are clinical recovery, cost-effectiveness, use of other diagnostic tests and medical services (including reconsultation), and patient enablement.

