#### Secondary outcome measures

1. Clinical recovery and return to usual activities

2. Cost-effectiveness of point of care CRP and communication training

3. Patient enablement, satisfaction and future consulting intention

4. Diagnostic testing other than point of care CRP

5. Use of health services, including re-consultation

6. Subsequent antibiotic prescribing rates within 28 days of the initial consultation

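### The slope of logged symptom scores is read as recovery speed, but with a floor at zero and at least 28 days of follow-up it does not rise steadily with recovery speed

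*Protocol article*

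**What the plan says.** The first secondary outcome in the protocol article is "Clinical recovery and return to usual activities". Under Data collection, "patients will be asked each day to complete a 6 item scale, with responses to statements ranging from 0 to 6", and "A total symptom score will be derived from this scale". On duration, "Patients will then be followed-up for 28 days, or if still unwell, until recovered with a maximum follow up of ten weeks"; the abstract likewise says "Patients will be followed up for at least 28 days".

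The Analysis section gives the model: "A four level linear regression model will be fitted to the symptom scores (logged) to account for practice, GP, patient and repeated assessments over time". Correlation between a patient's assessments is to be stronger for days closer together. The effect is then "seen in the comparison of the slopes of symptom scores over time in the groups, i.e. having faster (or slower) recovery rates". The sensitivity analyses described for this outcome deal only with loss to follow-up, and one of them reuses the fitted slope. The article describes no other analysis of symptom recovery. It does not give an expected recovery time, the treatment of zero scores before logging, or whether the groups share a starting level.

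**The concern.** A slope measures recovery speed only while scores are still falling. Once a patient is well, the score stays at 0, and every further diary day pulls a straight line towards the horizontal. A patient well after one week contributes about three weeks of zeros. A patient who improves evenly for two and a half weeks contributes a long decline and looks steeper. Logging does not remove this: it straightens an exponential decline only where there is no floor, and zeros need an offset before they can be logged. Beyond day 28, diary days come only from patients who are still unwell, so the observation window itself depends on the outcome.

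The trial aims to reduce prescribing without harming recovery, and this outcome carries the second half of that claim. A measure that cannot separate fast from moderate recovery, or that ranks them wrongly, would weaken the reassurance the trial is meant to provide.

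**Working it through.** The article states no slope, recovery time or power for this outcome, so there is no figure to reproduce.

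**Inputs from the article:** six items scored 0 to 6 (a sum would run 0-36; summing is assumed); daily diary; 28 days for all, and up to ten weeks if still unwell; linear model on logged scores; effect read from group slopes.

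**Assumed, because not given:** starting total 20, integer scores, offset of 1 before logging, shape of decline, distribution of recovery times.

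**Step 1: a single curve.** Let the score be 20 on day 1, fall evenly to 0 on day D (rounded to whole numbers), then stay at 0. With y = ln(score + 1) and t = 1 to 28, the least-squares slope is

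b = Σ(t − 14.5)·y / Σ(t − 14.5)², where Σ(t − 14.5)² = 28 × (28² − 1)/12 = 1827.

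For D = 7 the scores are 20, 17, 13, 10, 7, 3, 0, 0, and so on.

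| Well by day | Numerator | Slope per day | Mean of y, days 1-28 |
|---|---|---|---|
| 7 | −164.30 | −0.090 | 0.52 |
| 14 | −253.62 | −0.139 | 1.08 |
| 18 | −264.53 | −0.145 | 1.38 |
| 28 | −165.85 | −0.091 | 2.17 |

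The slope is steepest near day 18, and recovery by day 7 is indistinguishable from recovery by day 28. Starting the decline from day 0 instead gives −0.085, −0.142 and −0.089 for days 7, 18 and 28. The raw score shows the same hump: −0.454 (day 7), −0.829 (day 20, the steepest), −0.747 (day 28). The mean of y over the window orders the four cases correctly.

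**Step 2: groups with separate intercepts.** Two groups of 200 patients, lognormal recovery times, 40 runs, ordinary least squares. The entries count the runs in which the faster group had the flatter slope.

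| Median recovery (days) | Linear decline, 28 days | Exponential, 28 days | Linear, extended if unwell | Exponential, extended if unwell |
|---|---|---|---|---|
| 6 vs 9 | 40 | 40 | 39 | 40 |
| 8 vs 12 | 40 | 40 | 26 | 39 |
| 10 vs 14 | 37 | 40 | 8 | 12 |
| 12 vs 16 | 15 | 40 | 2 | 3 |
| 14 vs 20 | 0 | 34 | 0 | 0 |
| 20 vs 28 | 0 | 0 | 0 | 1 |

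At 6 vs 9 days (linear, 28 days) the mean slopes were −0.091 for the faster group and −0.110 for the slower.

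**Step 3: mixed model with random slopes, no serial correlation.** With exponential decline, median recovery of 25, 19, 15, 13 and 9 days gave slopes of −0.092, −0.092, −0.090, −0.085 and −0.071. From 19 to 9 days the slope flattens by (0.092 − 0.071)/0.092 = 23%. The mean log score fell steadily: 1.30, 1.00, 0.79, 0.68, 0.50.

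**Step 4: serial correlation, as the Analysis section requires.** Generalised least squares, separate intercepts, lag-1 correlation of 0 or 0.9 (assumed values), median 19 vs 9 days:

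- Exponential: −0.094 vs −0.071 at 0, a flattening of 0.023/0.094 = 24%; −0.097 vs −0.090 at 0.9, a flattening of 0.007/0.097 = 7%.
- Linear: −0.108 vs −0.099 at 0 (wrong order); −0.100 vs −0.105 at 0.9 (right order).

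For linear decline at 0.9, medians from 6 to 15 days gave slopes only between −0.107 and −0.111, so the slope barely distinguishes them.

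**Step 5: common intercept.** Forcing both groups to the same starting level in the least-squares fits gave the right sign on average in every scenario of Step 2 (differences from −0.005 to −0.035). With serial correlation of 0.7 or 0.9 the sign also stayed right.

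**The case against.** The strongest reply is that the wrong sign needs several conditions together: a straight line over the whole period, separate group intercepts, recovery mostly within about two weeks, and weak serial correlation. The article states that serial correlation will be modelled, and the large reversals in Steps 2 and 3 leave it out. The diary begins after the index consultation, so a common starting level would be a natural choice, and it removes the wrong sign. A linear mixed model can also carry curved time terms, which a full analysis plan would normally specify. The article gives no recovery times, and 19 vs 9 days is a very large assumed contrast. Return to usual activities, time off work and re-consultation also bear on recovery.

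Most of this stands as a limit on size and certainty. A reader might infer that the planned analysis will report faster recovery as slower, or that no time-to-recovery analysis exists. The documents support neither: the first depends on unstated inputs, and a condensed article cannot show the second.

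What remains is the reading rule that the article does state. Strong serial correlation makes the slope nearly insensitive rather than informative, and reversal persists for very early recovery with exponential decline. The article itself calls acute bronchitis generally self-limiting, so many zeros before day 28 are plausible.

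**Conclusion.** The point holds in limited form. Under the stated rule, the slope of logged scores over the full follow-up is not monotone in recovery speed. If most patients recover within roughly two weeks and the groups have separate intercepts, a faster group can show an equal or flatter slope. The flattening is about 23% without serial correlation for a fall in median recovery from 19 to 9 days, and about 7% with an assumed lag-1 correlation of 0.9. With linear decline the order at that correlation is right, but the slopes hardly differ across early recovery times. With later recovery, or with a common intercept, the sign was right in the simulations.

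These figures rest on an assumed starting score, offset, curve shape and recovery-time distribution. Severity is moderate: one secondary outcome is affected, and the primary prescribing analysis and the sample size are not. A reader might infer that the direction of the trial's recovery conclusion is bound to be wrong; the evidence does not go that far.

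**What to change.** Remove the statement that the full-period slope measures recovery speed. From the diary already planned, analyse one or both of:

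- time to recovery, with the threshold fixed before data are seen, censoring at the last diary day (ten weeks at most) and practice clustering in the model;
- the mean symptom score over one fixed window that is the same for every patient.

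If the slope is kept, give the groups a common baseline, state how zeros are handled, and either restrict it to an early fixed window or use piecewise or non-linear time.

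The cost is wording, a little more analysis, and an advance choice of threshold or window. No new data are needed.
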